### Myo-inositol group

Participants will be instructed to ingest 6 g of myo-inositol (or its placebo) in water each morning for 12 weeks.

### Outcomes

Ovulation is the primary outcome (categorical “yes” or “no”) and frequency of ovulation (nominal “0”, “1”, “2”, or “3”) during the 12-week (84-day) study. The study length allows observation of three potential ovulatory cycles. The upper limit of a normal ovulatory cycle length is 35 days, hence, to document ovulation using progesterone levels in the expected luteal phase, the study may extend to the end of week 14. Ovulation will be identified by assessing the serum progesterone level on day 22 and, if appropriate, will be repeated 1 week later. A progesterone level greater than 10 nmol/L will be used to confirm ovulation. The secondary outcome is conception (categorical “yes” or “no”). Other outcomes that will be evaluated are miscarriage rates, changes in numerical scores of depression, anxiety, stress, and quality of life based on the DASS and the FertiQoL.

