**Methods/design:**

This is a randomized controlled trial which will include 240 women diagnosed with PCOS, according to the Rotterdam criteria, who are trying to conceive. Participants will be randomized to either a comprehensive lifestyle intervention program or prescribed an oral fertility medication, letrozole. These two groups will be further randomized to consume either myo-inositol or a placebo. Participants will be between the ages of 18 and 37 years. Exclusion criteria include women who have already begun fertility treatment, who are currently using myo-inositol or have taken it within the past 3 months, or who are being treated for, or have a history of, an eating disorder. The primary outcome will be the ovulation rate, the secondary outcome will be conception. Other outcomes include miscarriage rates, validated rating measures of overall quality of life (including social, relational, mind/body and emotional sub-categories) and mental health scores (depression, anxiety, and stress).

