## Background

Polycystic ovary syndrome (PCOS) is a heterogenous endocrine syndrome characterized by chronic anovulation and hyperandrogenism (clinical or biochemical) according to the original 1990 NIH criteria. The 2003 Rotterdam criteria added the presence of polycystic ovarian morphology on ultrasound which resulted in four distinct PCOS phenotypes. PCOS is also associated with obesity, insulin resistance, metabolic syndrome, reduced quality of life, increased anxiety and higher rates of depression [1]. Between 70 and 80% of women with PCOS have difficulty conceiving due to oligo- or anovulation. Despite ovulation rates of 75–80% achieved with the use of ovulation-induction agents and a conception rate per cycle of 22% (comparable to that of a healthy women trying to conceive naturally in their first year), some women with PCOS remain unresponsive [2, 3]. In contrast, evidence suggests that lifestyle (diet, activity and stress management) influences ovulation and the effectiveness of fertility treatments [4–6].

While lifestyle intervention is recommended as first-line management for women with PCOS and obesity, 45% of women with PCOS reported that they have never received information on lifestyle management and only 61–76% of reproductive endocrinology and infertility obstetric gynecologists (REI-ObGyn) and 46–61% of obstetric gynecologists (ObGyn) recommended lifestyle modifications to patients for fertility or non-fertility problems [7, 8]. Even with efforts to improve dietary and exercise habits, women with PCOS often have difficulty managing their weight. In addition, 62% of women with PCOS reported never receiving information about emotional support or counseling [7]. It appears that attention to general physical and psychological health is inconsistent at the clinical level yet recognized as an important factor in the effective management of women receiving the life-altering diagnosis of PCOS and/or infertility [9, 10].

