### Letrozole group

The use of clomiphene citrate has been commonly used to treat anovulatory infertility. However, clinical experience and recent study evidence has suggested that letrozole is more effective than clomiphene citrate in achieving ovulation in PCOS [29]. Additionally, letrozole does not negatively affect endometrial thickness. The initial dose will be 5 mg daily for 5 days which can be increased to a total daily dose of 7.5 mg, if necessary, depending on the ovulatory response as per current clinical practice at the Grace Fertility Centre. The first dose will be defined as “cycle day 3” which corresponds to cycle day 3 of spontaneous menses or day 3 of an induced withdrawal bleed following progestogen withdrawal. This treatment regimen will continue for three cycles or until pregnancy is achieved. Subjects will be advised to have intercourse every other day during the expected ovulatory period (beginning cycle day 12, for a week) and to use urinary ovulation prediction kits.

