## Statistical methods

The participants’ biochemical and hormonal profiles, physical attributes (body mass index (BMI), hirsutism), ovulatory response, pregnancy status, scores for depression, anxiety, stress and quality of life will be assessed for statistical normality. Each main effect will be compared by analysis of variance (ANOVA) or its non-parametric equivalents. The primary comparison will be between GLC and letrozole. The observed effects of myo-inositol alone are small in clinical experience and there are no reported interactions between myo-inositol and ovulation-induction medications or lifestyle change in the literature. Hence, our power calculations (see below) have been based on the two main effects acting independently. However, our factorial design will provide an opportunity to explore potential interactions (acknowledging the sample size required would change in the presence of interactions) [30, 31]. Categorical data will be compared by chi-square statistics. Differences in dietary intake and dietary composition over time will be compared by ANOVA or its non-parametric equivalent with time as the repetitive measure. Regression analysis will also be performed to determine the individual impacts of diet, activity, and mindfulness on ovulation. In addition, membership in the four PCOS sub-groups will be further explored as a potential predictor for ovulation rates in regression analysis after adjusting for BMI and age.

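### The primary outcome joins a powered yes/no ovulation measure to a raw 0–3 count that conception cuts short; the count should be secondary and analysed per cycle at risk

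*Protocol article*

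**What the plan says.** - **Outcomes.** One sentence holds both forms. It opens "Ovulation is the primary outcome (categorical", with values yes or no, and continues "and frequency of ovulation (nominal", with values 0, 1, 2 or 3. It adds that "The study length allows observation of three potential ovulatory cycles". Conception, yes or no, is the secondary outcome.
- **Abstract, Methods/design.** A single primary outcome is named: "The primary outcome will be the ovulation rate, the secondary outcome will be conception".
- **Letrozole group.** "This treatment regimen will continue for three cycles or until pregnancy is achieved". No such sentence appears for the lifestyle arm, where pregnancy itself ends the run of cycles.
- **Statistical methods.** "Categorical data will be compared by chi-square statistics". The same section compares each main effect by ANOVA or a non-parametric equivalent and includes ovulatory response among the variables to be checked for normality.
- **Sample size and power calculations.** Two proportions, 5% level, 80% power; 70% against 50% gives 182 in total, 91 per group.

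The article does not say which of the two forms decides the trial.

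**The concern.** A woman who conceives in her first cycle can score at most 1 (early pregnancy loss aside). A woman who ovulates three times without conceiving scores 3. On a raw count the better clinical result ranks lower, and how often that happens depends on each arm's conception rate. The arms are a lifestyle programme and an ovulation-induction drug, so equal conception per ovulation cannot be taken for granted.

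Two smaller matters come with this. The count is ordered, but it is labelled nominal, and a test that follows the label discards the order. The count also stands beside the yes/no form under the primary outcome, although only the yes/no form is powered and only one 5% level is stated.

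At stake is whether a result on ovulation frequency can be read as a result on ovulation.

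**Working it through.** **The plan's own figure.** With the unpooled two-proportion formula and two-sided 5%:

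n = (1.960 + 0.842)² × [0.70×0.30 + 0.50×0.50] / 0.20² = 7.849 × 0.46 / 0.04 = 90.3, so 91 per group and 182 in total. This reproduces exactly, for the yes/no form only. No figure is given for the count.

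**Inputs for the count.** Three cycles (Outcomes). Rates of 70% and 50% (Table 1), which the article does not label as per cycle or per woman. 22% conception, which Background gives per cycle; applying it per ovulatory cycle is an assumption. All other rates below are assumptions.

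**Expected count.** With ovulation probability p per cycle, conception probability c per ovulatory cycle, independent cycles, and counting stopped at conception:

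E = p × [1 + (1 − pc) + (1 − pc)²]

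*Equal conception, c = 0.22, against no conception:*

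- 70% and 50% read as per-cycle rates. Without conception: 2.10 − 1.50 = 0.60. With it: 1.79 − 1.34 = 0.45. The difference shrinks by 25%.
- 70% and 50% read as per-woman rates over three independent cycles. Then p = 1 − 0.30^(1/3) = 0.331 and 1 − 0.50^(1/3) = 0.206. Without conception: 0.99 − 0.62 = 0.37. With it: 0.92 − 0.59 = 0.33. The difference shrinks by about 11%.

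*Unequal conception:*

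- p = 0.70 in both arms. The mean count is 1.96 at c = 0.10 and 1.69 at c = 0.30. The chance of at least one ovulation is 1 − 0.30³ = 0.973 in both.
- p = 0.70 with c = 0.30, and p = 0.60 with c = 0.10, both give a mean of 1.69. A true gain in ovulation disappears.

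**False positives.** Simulation with 91 per arm, equal ovulation of 60% per cycle, within-woman correlation 0 to 0.5:

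| Analysis | c = 22% vs 11% | c = 22% in both |
|---|---|---|
| 0–3 count, 3-df chi-square | 13–17% | about 5% |
| 0–3 count, rank test | 14–16% | about 5% |
| Ovulations per cycle at risk, robust variance | 5–6% | about 5% |
| Ovulation yes/no | about 5% | about 5% |

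The excess comes from truncation and not from the choice of test.

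**Ignoring order.** Power at 70% vs 50% per cycle, c = 0.22, 91 per arm, chi-square against rank test: about 91% vs 95% at correlation 0, 80% vs 88% at 0.25, and 71% vs 82% at 0.5. The loss is about 4 to 11 points.

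**Two forms, each at 5%.** With no true difference and equal conception, at least one of yes/no and the chi-square on the count is significant in about 8% of trials. The bound for independent tests is 1 − 0.95² = 9.75%; the two forms are strongly related, so the actual figure is lower.

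**The case against.** Several stronger readings are tempting, and the article does not support them.

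- *The count will be tested by a nominal chi-square.* A reader might infer this from the label and the sentence on categorical data. But Statistical methods also allows ANOVA or a non-parametric test and lists ovulatory response among the variables checked for normality, and nominal may be a slip for numerical. The test is not fixed, and choosing it is commonly left to the SAP. The power loss therefore applies only if the label is followed.
- *The count penalises whichever arm has more pregnancies.* This is conditional. With equal conception per ovulation, the arm that ovulates more also conceives more and still stays ahead (1.79 against 1.34). Its lead is diluted, and there is no excess of false positives. An excess needs conception per ovulation to differ, and no passage supports the assumed 11%.
- *The trial takes two chances at a primary claim.* No either/or rule is stated. The abstract names one ovulation rate and the power calculation covers one comparison. The 8% follows only from one reading of the Outcomes sentence.

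It can also be said that how to count cycles after conception is a detail for the SAP. That stands for the counting rule alone. It does not cover the choice of a raw 0–3 scale under the primary outcome, which the article itself makes. The powered yes/no form is unaffected, provided conception is accepted as evidence of ovulation.

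**Conclusion.** The point holds in a limited form. The Outcomes section puts an unpowered raw count beside the powered yes/no form, and conception truncates that count.

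At equal conception per ovulation, the cost is a difference diluted by about 11% to 25%, depending on whether 70% and 50% are per-woman or per-cycle rates, with 22% conception taken per ovulatory cycle. If conception per ovulation differs between arms, the count is no longer a valid comparison of ovulation: about 13–17% false positives at an assumed 22% against 11%, whether a chi-square or a rank test is used. The nominal label and the joint primary wording are lesser faults, costing respectively 4 to 11 points of power if the label is followed and an overall error of about 8% if either form may carry the claim.

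None of this touches the yes/no comparison or its sample size. The change should be made, and Trial status says that recruitment has not begun.

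**What to change.** - Name ovulation yes/no per woman as the sole primary outcome and state that conception counts as ovulation. This matches the power calculation and leaves the 182 unchanged.
- Make frequency of ovulation a secondary outcome. Define it as ovulations per cycle at risk, excluding cycles after conception, and analyse it with a variance that allows for within-woman correlation (a binomial GEE, or a ratio with cycles at risk as denominator and a robust standard error).
- Drop the nominal label and do not analyse the raw 0–3 count as unordered categories.

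The cost is a change of wording in Outcomes and Statistical methods, with no extra participants or measurements. The downside is that frequency can no longer support a primary claim.

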## Statistical methods

The participants’ biochemical and hormonal profiles, physical attributes (body mass index (BMI), hirsutism), ovulatory response, pregnancy status, scores for depression, anxiety, stress and quality of life will be assessed for statistical normality. Each main effect will be compared by analysis of variance (ANOVA) or its non-parametric equivalents. The primary comparison will be between GLC and letrozole. The observed effects of myo-inositol alone are small in clinical experience and there are no reported interactions between myo-inositol and ovulation-induction medications or lifestyle change in the literature. Hence, our power calculations (see below) have been based on the two main effects acting independently. However, our factorial design will provide an opportunity to explore potential interactions (acknowledging the sample size required would change in the presence of interactions) [30, 31]. Categorical data will be compared by chi-square statistics. Differences in dietary intake and dietary composition over time will be compared by ANOVA or its non-parametric equivalent with time as the repetitive measure. Regression analysis will also be performed to determine the individual impacts of diet, activity, and mindfulness on ovulation. In addition, membership in the four PCOS sub-groups will be further explored as a potential predictor for ovulation rates in regression analysis after adjusting for BMI and age.

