### Sample size and power calculations

Assuming no interactions between the two main effects as discussed earlier, the target sample size will be 240 participants (120 participants in the GLC group and 120 participants on oral medication). This is based on: a power calculation using a 5% significance level, 80% power comparing two proportions, and current knowledge of the average ovulation rates of lifestyle interventions and letrozole, our primary comparison. We explored a number of combinations of the ovulation rates from letrozole and lifestyle interventions and chose the most conservative estimate to ensure that our sample size was adequate, i.e., 91 in each group. By enrolling 120 participants in each group, we have allowed for a drop-out rate of 32%. Table 1 describes the lowest and highest reported ovulation rates for letrozole and lifestyle interventions, the sample size required in each scenario comparing the two proportions, and the three highest sample sizes required from our calculations, accounting for the length of lifestyle intervention and the start dose of letrozole.

**Table 1 Tab1:** Sample size calculation based on previous literature

Range of reported ovulation rates	Letrozole ovulation rate	Lifestyle ovulation rate	Total sample size needed
Lowest	62%^a^	38%^b^	130
Highest	86%^c^	67%^d^	150
Median	70%	50%	182

^a^Legro et al. [29]

^b^Palomba et al. [36]

^c^Zeinalzadeh et al. [37]

^d^Karimzadeh and Javedani [38]

When calculating the sample size necessary to assess the effect of myo-inositol on ovulation rates, we reviewed the few published studies available acknowledging that these studies all had small sample size. One randomized controlled trial reported an ovulation rate of 70% when myo-inositol was given to women with PCOS versus a 21% ovulation rate in controls [24]. Similarly, another randomized controlled trial reported an ovulation rate of 65% using myo-inositol in PCOS [32]. Using these rates in a comparison of two proportions, a total sample size of 26 is needed, and easily covered by our original calculation above.

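### Ovulation and conception are assigned only an unadjusted chi-square, and DASS and FertiQoL are defined as changes; this gives away precision and an adjusted effect estimate

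*Protocol article*

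**What the plan says.** The trial is a 2×2 factorial (Overall study design): 1:1 to the lifestyle programme (GLC) or letrozole, then 1:1 within each group to myo-inositol or placebo. Under Outcomes, ovulation is primary (yes/no, with a count of 0 to 3) and conception is secondary (yes/no).

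Statistical methods states:
- "ovulatory response, pregnancy status, scores for depression, anxiety, stress and quality of life will be assessed for statistical normality" (the list also covers biochemical and physical measures);
- "Each main effect will be compared by analysis of variance (ANOVA) or its non-parametric equivalents";
- "Categorical data will be compared by chi-square statistics".

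BMI and age enter as covariates once, in a regression that explores PCOS phenotype as a predictor of ovulation. A second regression relates ovulation to diet, activity and mindfulness. Neither is described as the model for a randomised comparison.

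Outcomes also lists "changes in numerical scores of depression, anxiety, stress, and quality of life based on the DASS and the FertiQoL". Data collection says that both questionnaires are completed before and after the 12-week programme.

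**The concern.** A chi-square of GLC against letrozole takes one factor and no covariates, and it yields a p-value rather than an adjusted effect with an interval. The authors evidently regard BMI and age as worth adjusting for, since they do so for phenotype, yet no model carries them into the main comparison. The factorial structure is to be used to explore interactions, but no model is named that would do this for the yes/no outcomes.

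For the questionnaires, a baseline score is available for every woman assessed at entry. An outcome defined as a change uses that score only by subtraction, which is less efficient than adjusting for it.

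Testing a yes/no variable such as pregnancy status for normality has no meaning.

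At stake is information the trial collects anyway, and how the main result will be expressed.

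**Working it through.** **1. The plan's own figure.** The inputs are "a power calculation using a 5% significance level, 80% power comparing two proportions" and the governing row of Table 1, "Median 70% 50% 182" (letrozole 70%, lifestyle 50%). Sidedness is not stated; two-sided is assumed. With unpooled variance:

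n per group = (1.960 + 0.842)² × (0.70×0.30 + 0.50×0.50) / 0.20² = 7.849 × 0.46 / 0.04 = 90.3, so 91 per group and 182 in total.

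This matches the article. No stated number is disputed here. Power at 91 per group is Φ(0.20/√(0.46/91) − 1.96) = 80.3%.

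**2. Baseline covariates for ovulation.** If covariates explain a share R² of the outcome variance, the variance of the risk difference is multiplied by about (1 − R²), and power is Φ(0.20/√(0.46(1 − R²)/91) − 1.96). The article gives no R², so the range is an assumption.

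| Assumed R² | Power, 91 per group | Power, 120 per group |
|---|---|---|
| 0 | 80.3% | 89.8% |
| 2% | 81.1% | 90.4% |
| 5% | 82.3% | 91.2% |
| 10% | 84.3% | 92.6% |

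At R² of 5% and 10%, 182 evaluable women carry the information of 182/0.95 ≈ 192 and 182/0.90 ≈ 202.

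**3. The second randomised factor for ovulation.** Take balanced factors and an additive myo-inositol effect d on the risk scale. The within-stratum variance is then 0.46 − d²/2. Stratified power is Φ(0.20/SE_s − 1.96) and unadjusted power is Φ((0.20 − 1.96·SE_m)/SE_s), with SE_s = √((0.46 − d²/2)/91) and SE_m = √(0.46/91).

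| Assumed d (points) | Variance reduction | Unadjusted power | Stratified power |
|---|---|---|---|
| 5 | 0.3% | 80.4% | 80.4% |
| 10 | 1.1% | 80.5% | 80.7% |
| 20 | 4.3% | 80.9% | 82.0% |
| 30 | 9.8% | 81.5% | 84.2% |
| 49 | 26% | 84.0% | 90.5% |

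The article points both ways on d. Statistical methods expects a small effect of myo-inositol alone, while Sample size and power calculations sizes that factor on 70% against 21%, which is 49 points.

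**4. DASS and FertiQoL.** Let r be the correlation of baseline with the 12-week score, with equal variance at both times. Per-woman variance is proportional to 2(1 − r) for a change score and 1 − r² for ANCOVA. The reduction from using ANCOVA is 1 − (1 − r²)/(2(1 − r)) = (1 − r)/2.

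| Assumed r | Change score | ANCOVA | Reduction |
|---|---|---|---|
| 0.3 | 1.40 | 0.91 | 35% |
| 0.5 | 1.00 | 0.75 | 25% |
| 0.7 | 0.60 | 0.51 | 15% |
| 0.8 | 0.40 | 0.36 | 10% |

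The article gives no r.

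**The case against.** The strongest reply is that nothing here is invalid. Both factors are randomised 1:1, the second within the first, so unadjusted comparisons are unbiased over randomisation and keep their type I error. The chi-square also matches the two-proportion power calculation, and a risk difference with an interval could be reported beside it. The gain for the primary outcome is modest and rests on an assumed R²; the larger gains concern outcomes that the article ranks below conception. An analysis plan that is not shown may name a better model. All of this stands, and it limits the point to efficiency and reporting.

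Several stronger readings are tempting, but the text does not support them:
- *The ANOVA ignores the second factor.* The sentence speaks of main effects in a factorial design, and the section plans to explore interactions, so it fits a two-way ANOVA. Only the chi-square sentence leaves the factor out.
- *ANOVA will be run on change scores.* This joins two sections. Outcomes defines changes; Statistical methods lists scores and does not say which quantity enters the ANOVA.
- *The rank-based fallback cannot handle two factors.* That holds for a one-way rank test, but the article names no particular test.
- *Change scores leave bias from regression to the mean.* Under randomisation this affects both arms equally in expectation. Chance imbalance costs precision and is not systematic bias.

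The normality wording is a minor slip. Ovulatory response may include the 0-to-3 count, and categorical data go to chi-square in any case, so no result changes.

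**Conclusion.** The point holds as a loss of precision and of an adjusted estimate, and not as an error that biases the trial. For ovulation and conception, the only test the article names uses neither the second factor nor baseline covariates. For DASS and FertiQoL, the outcome is defined as a change and no baseline-adjusted model is named, although baseline is measured.

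The size depends on quantities that the article does not give. For ovulation it is about 2 to 4 power points at R² of 5–10%. The second factor adds about 1 point or less unless the myo-inositol effect exceeds 20 points; only at the cited 49 points does it reach about 6.5. For the scores, the variance reduction is 15–35% over correlations of 0.7 to 0.3. The case for changing the plan is that the improvement is nearly free, not that the present plan would fail.

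**What to change.** - **Ovulation (yes/no) and conception:** for each, fit one logistic model with GLC/letrozole, myo-inositol/placebo, BMI and age. Report a standardised (marginal) risk difference with a 95% confidence interval for each factor; the precision gain shown above applies on that scale. Keep the interaction as an exploratory term.
- **Specify BMI before randomisation.** The Background expects the lifestyle programme to restore ovulation partly through weight loss, so adjusting for a later BMI would remove part of the effect being estimated.
- **DASS and FertiQoL:** analyse the 12-week score by ANCOVA with the baseline score and both factors. Do the same for any hormonal or metabolic measure that has a baseline value; the article's text does not give the timing of those measures.
- **Normality:** delete the check for yes/no outcomes.

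The cost is analysis wording, provided that BMI is recorded before randomisation, which should be confirmed. Trial status says recruitment had not begun, so the change can be fixed in advance without sight of any data.

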### Lifestyle intervention group (GLC)

The GLC group will have weekly check-ins with physicians and educators for 12 consecutive weeks. A wellness booklet designed and provided by clinicians will outline the main concepts being taught. Each week, subjects will receive detailed comprehensive instructions on how to follow a low-glycemic meal plan, incorporate walking 10,000 steps a day, and induce the relaxation response using cognitive behavioural therapy techniques. The low-glycemic-meal plan requires participants to consume 45% of carbohydrates in their diet and no more than 55 g of glycemic load a day, which is similar to previous low-glycemic diet intervention studies. Lists will be provided outlining foods that are low, medium, or high in their glycemic load. Hence, within their overall meal plan, participants will be advised to eat predominantly low-glycemic foods and to limit high-glycemic foods. They will also be provided with a pedometer to record the number of steps taken each day. These steps can be achieved by any form of exercise that participants can sustain. Lastly, participants will practice relaxation response exercises for 20 min daily on their own, in combination with 6 weeks of mindfulness training provided within the 12-week intervention program.

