### Potential biases or limitations

The drop-out rate is often high in lifestyle-based interventions. To mitigate a high drop-out rate we have taken steps such as providing daily email contacts and weekly check-ins between participants and health care providers throughout the duration of the study (12 weeks). A lack of compliance can often become another limitation for intervention studies. To ensure compliance of participants, especially with the lifestyle modification group, we will provide weekly in-person education sessions, as well as periodic check-ins over the phone, in order to explain and reinforce the importance and significance of the recommendations provided and how our study participants might directly benefit from such comprehensive lifestyle changes. These weekly sessions will provide an opportunity for participants to ask questions and receive support from both clinicians and other women struggling with similar issues. After each session, the participant’s weight will be recorded (in a private setting) to help them remain motivated in adhering to the dietary changes and increased physical activity. Several dietary recall methods will be used to measure compliance to the low-glycemic diet, such as a 24-h recall and a food frequency questionnaire, recognizing these tools also have their own limitations.

Although the main goal of this intervention is to achieve a pregnancy, improving overall health and quality of life for women with PCOS is an important component in achieving this primary goal. Infertility per se has a significant psychological impact on women, as does the diagnosis of PCOS. Failed repetitive cycles of hormone therapy further adds to stress and reduced quality of life in PCOS, providing a rationale to develop a comprehensive support program for sustainable lifestyle changes. In addition to improving ovulatory function and the chance of conceiving, such a program has the potential to enhance long-term physical and mental health in this population.

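### GLC is partly delivered in sessions shared between women, but the chi-square test and the 91 per group assume independence; any positive within-session correlation would make the GLC-versus-letrozole test anti-conservative and the 80% power optimistic

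*Protocol article*

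**What the plan says.** **Delivery.** Under Overall study design, individual women are randomised 1:1 to GLC or to letrozole with usual physician counselling. The GLC section describes weekly contact with physicians and educators for 12 weeks, "in combination with 6 weeks of mindfulness training provided within the 12-week intervention program". Potential biases or limitations adds that there are weekly in-person education sessions and says of them: "These weekly sessions will provide an opportunity for participants to ask questions and receive support from both clinicians and other women struggling with similar issues". No sessions are described for the letrozole arm.

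**Analysis.** Statistical methods makes GLC versus letrozole the primary comparison. Ovulation (yes/no) is the primary outcome, and for such data the section states: "Categorical data will be compared by chi-square statistics". It discusses independence only between the two factorial effects, not between women who share sessions.

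**Sample size.** The calculation is "a power calculation using a 5% significance level, 80% power comparing two proportions". The authors "chose the most conservative estimate to ensure that our sample size was adequate, i.e., 91 in each group", which is the Table 1 row "Median 70% 50% 182". Planned enrolment is "120 participants in the GLC group and 120 participants on oral medication".

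**The concern.** When women in one arm meet each week with other participants and support one another, their outcomes may be more alike than those of women treated separately. The result is a partially nested design, with clustering in the GLC arm only. A chi-square test that counts every woman as independent would then use too small a variance for the GLC proportion, and a two-proportion sample size would be too small for a test that uses the right variance.

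The p-value and confidence interval for the primary comparison are at stake, and so is the 80% power claim. The same applies to conception, DASS and FertiQoL in the comparison of GLC with letrozole. The myo-inositol comparison is largely unaffected, because women on active supplement and on placebo are both present within GLC.

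**Working it through.** **Inputs from the protocol.** Significance level 5% (sidedness not stated, two-sided assumed); power 80%; rates 70% (letrozole) and 50% (lifestyle); 91 evaluable and 120 enrolled per group.

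**Inputs assumed.** Session-group size m (6 to 15) and ICC (0 to 0.10). The protocol gives neither.

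**Step 1: reproduce the plan's figure.** Unpooled two-proportion formula:

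n = (1.960 + 0.842)² × [0.70×0.30 + 0.50×0.50] / 0.20² = 7.849 × 0.46 / 0.04 = 90.3, so 91 per group, 182 in total.

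The same formula returns the other two Table 1 totals exactly (130 and 150). The published sizes are therefore independent-samples figures with no design effect. By the pooled formula used below, power at 91 per group is 79.1%, so the baseline here is 79%.

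**Step 2: GLC design effect.** DE = 1 + (m − 1) × ICC for GLC, and 1 for letrozole. With m = 10 and ICC 0.05, DE = 1 + 9 × 0.05 = 1.45.

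**Step 3: type I error of the unadjusted chi-square.** With equal arms, the true standard error exceeds the assumed one by √((1 + DE)/2):

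α = 2 × [1 − Φ(1.96 / √((1 + DE)/2))]

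For DE = 1.45: √1.225 = 1.107; 1.96/1.107 = 1.771; α = 7.7%. A beta-binomial simulation (100,000 runs, common rate 60%, 91 per group) gave 7.6%.

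**Step 4: power of a test that uses the right variance.**

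Power = Φ{ [0.20 − 1.96 × √(0.24 × (1 + DE)/n)] / √((0.21 + 0.25 × DE)/n) }

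For n = 91 and DE = 1.45: (0.20 − 0.1575)/0.0793 = 0.535, so power is 70%. For n = 120 it is 82%. A simulated cluster-robust t test with Satterthwaite degrees of freedom at n = 91 held type I error at 5.4% and had 67% power.

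**Step 5: range** (formula results)

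| ICC | m | Chi-square type I error | Adjusted power, 91 per group | Adjusted power, 120 per group |
|---|---|---|---|---|
| 0 | any | 5.0% | 79% | 89% |
| 0.01 | 6-15 | 5.3-5.8% | 76-78% | 87-88% |
| 0.05 | 6 | 6.5% | 74% | 85% |
| 0.05 | 10 | 7.7% | 70% | 82% |
| 0.05 | 15 | 9.2% | 66% | 78% |
| 0.10 | 10 | 10.4% | 63% | 75% |

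In the last row, small-sample degrees of freedom lower the 63% to about 58%. The unadjusted chi-square itself loses little power at 91 per group (77% at m = 10, ICC 0.05). Most of the power loss appears once the test is made valid.

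**Step 6: interval width.** At m = 10 and ICC 0.05 the interval for the difference widens by √((0.21 + 0.25 × 1.45)/(0.21 + 0.25)) = √(0.5725/0.46) = 1.12, about 12%, before any small-sample correction.

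**The case against.** A reader might infer that the false-positive rate does exceed 5% and that 80% power will not be delivered. The documents do not support that. Both statements need a positive ICC and a session size, and neither is given.

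Further points against a strong reading:

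- **Group structure is unclear.** Nothing says that GLC runs in closed cohorts or that the mindfulness training is given in groups. With rolling entry, 1 + (m − 1) × ICC is only an approximation. This stands.
- **Much of GLC is individual.** Relaxation is practised alone, steps are counted by each woman's own pedometer, and diet recalls are by telephone. Ovulation is defined by serum progesterone. The correlation for the primary outcome may well be small. This stands, though less so for DASS and FertiQoL, where shared support is a plausible route of effect.
- **The plan has some reserve.** It uses the most demanding Table 1 row. With m = 10, ICC 0.05 and 91 per group, the Step 4 formula gives about 84% for 62% versus 38% and 78% for 86% versus 67%. Enrolment is also 120 per group. This stands in part: the extra enrolment is meant to cover drop-out, which the protocol itself expects to be a problem in lifestyle interventions, so the 82% at 120 requires almost none.
- **Variance details belong in a statistical analysis plan.** This is fair for the choice of model and degrees of freedom. However, the article does fix the chi-square test and a power statement that rests on independence.

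**Conclusion.** The point holds in conditional form. The protocol describes sessions shared by women in one arm only, while its named test and its sample size treat all women as independent. For any positive within-session correlation, the chi-square for GLC versus letrozole is anti-conservative and the 80% at 91 per group is optimistic.

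The size is an assumption. There is no effect at ICC 0 and a small one at ICC 0.01. At ICC 0.05 with groups of 10 the effect is material: about 7.7% type I error and 70% power at 91 per group. It is larger at ICC 0.10: about 10% and 58-63%. The documents do not show which of these applies. They give enough reason to collect session membership and allow for it, but they do not establish that the error rate is inflated or that the trial is underpowered.

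**What to change.** 1. Record each GLC woman's session group: her start cohort, or her main group if entry is rolling. The protocol says recruitment has yet to begin, so this can be in place from the first participant. It may be hard to reconstruct later.
2. For ovulation, conception, DASS and FertiQoL, compare GLC with letrozole using a variance that allows for session group in the GLC arm only. Suitable choices are a partially nested model (logistic for the binary outcomes, linear for the scores), or a cluster-robust variance with small-sample degrees of freedom and each letrozole woman as her own cluster.
3. In Sample size and power calculations, say that the 80% assumes independence within GLC, and add the power at 91 evaluable per group over a stated range of ICC and session size.

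The cost is one extra recorded variable and changed wording, with no extra patients or procedures. The downside is a slightly wider confidence interval and a less favourable stated power. If the correlation proves close to zero, little is lost.
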